### Sample size calculation

In an earlier study performed with older adults, the standard deviation for the primary outcome was shown to be 1.4 for COPM performance and 1.6 for COPM satisfaction [33]. The current trial is a multicenter study with 44 participating municipalities, so we expect that the variation in the COPM scores will be larger, and thus we employ a conservative estimate of 2.5 for the standard deviation. Furthermore, the allocation of participants to the intervention group or control group will not be randomized, and the number of participants in the intervention group will probably be three to four times that in the control group. We aim to detect a change of one point as statistically significant at a two-sided 5 % level and with a power of 80 %. Based on these estimates, sample size calculations indicate that we need to include 70 participants in the control group and 260 in the intervention group. Therefore, to consider the possibility of a relatively high dropout rate (up to 35 %) due to frail participants, a minimum of 107 and 400 participants will be included in the control and intervention groups, respectively.

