## Methods/design

### Design and setting

This will be a large multicenter clinical controlled trial. The study will be conducted in primary care settings in 44 of the 428 Norwegian municipalities, including eight municipalities that function as a control group; for three municipalities with two zones, one will be assigned to the control group and the other to the intervention group (see Fig. 1 for flow diagram). The allocation of zones to the intervention or control group was based on practical reasons and decided by the municipality. The municipalities included represent 17 % of the total population in Norway. The experimental group will be offered reablement and the control group standard treatment. The sample will comprise approximately 750 participants, who will be assessed at baseline and after 10 weeks, 6 months, and 12 months.

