### Statistical analysis

The data are suitable for multilevel or hierarchical modeling. Individuals are nested within municipalities and municipalities will be treated as fixed effects when mixed-effects models are applied.

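### The sample size has no design effect for allocation by municipality, so the stated 80% power at 70 and 260 participants is not assured once the ICC exceeds about 0.02

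*Protocol article*

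**What the plan says.** The Sample size calculation section takes a one-point difference on the COPM, a two-sided 5% level, 80% power and an intervention arm three to four times the size of the control arm. An earlier study gave SDs of 1.4 (performance) and 1.6 (satisfaction). These are raised for the multicenter setting: "The current trial is a multicenter study with 44 participating municipalities, so we expect that the variation in the COPM scores will be larger", and so "we employ a conservative estimate of 2.5 for the standard deviation". The result is that "sample size calculations indicate that we need to include 70 participants in the control group and 260 in the intervention group". With up to 35% dropout, "a minimum of 107 and 400 participants will be included in the control and intervention groups, respectively".

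The section gives no intracluster correlation (ICC), cluster size or design effect.

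Elsewhere the article describes a clustered design. Design and setting has 44 municipalities, eight of them control, and three divided into a control zone and an intervention zone. The same section says: "The sample will comprise approximately 750 participants". Statistical analysis states: "Individuals are nested within municipalities".

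**The concern.** Where treatment goes to whole municipalities or zones, participants in one unit share its services, staff and case mix, and their scores tend to be alike. The article expects this: it says that both standard care and the intervention will vary between municipalities. The precision of the comparison then depends heavily on the number of control units, which is small.

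The section recognises municipality variation but enters it as extra individual SD. The formula then divides it by 70 control participants, when it really averages out over only 8 to 11 control units.

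At stake is how a null result is read. Someone relying on the stated 80% could take it as adequately powered evidence of no one-point difference, although the calculation behind that figure does not fit the design.

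**Working it through.** **Inputs from the protocol article.** Difference 1; SD 2.5; two-sided 5% (z = 1.960); power 80% (z = 0.842); analysed 70 control and 260 intervention; dropout 35%; planned total about 750. Depending on how the three divided municipalities are counted, there are 8 to 11 control and 36 to 39 intervention units.

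**Assumptions.** ICC of 0.01 to 0.10; equal cluster sizes; a random municipality effect; 36 intervention units (using 39 moves no figure below by more than half a point).

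**1. The plan's own figure, participants independent.** Control n = (1.960 + 0.842)² × 2.5² × (1 + 70/260) = 7.849 × 6.25 × 1.269 = 62.3. Allowing for the t distribution, this is 63 control and 234 intervention. At 70/260, SE = 2.5 × √(1/70 + 1/260) = 0.337, and power = Φ(1/0.337 − 1.960) = 84.4%. So the stated numbers are somewhat larger than needed under independence and leave about four points of slack.

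**2. Why a larger SD is not a design effect.** Within-municipality variance is multiplied by 1/70 + 1/260 = 0.0181. Between-municipality variance is multiplied by 1/8 + 1/36 = 0.1528, or by 1/11 + 1/36 = 0.1187 with 11 control units. The same amount of variance therefore counts about 8.4 or 6.5 times as much when it lies between municipalities as when it is entered as individual noise.

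**3. Power with clustering.** SE² = SD² × [DE(control)/n(control) + DE(intervention)/n(intervention)], with DE = 1 + (m − 1) × ICC and m = participants per unit in that arm.

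At ICC 0.05:
- control DE = 1 + (70/8 − 1) × 0.05 = 1.39, or 1.27 with 11 units
- intervention DE = 1 + (260/36 − 1) × 0.05 = 1.31
- SE = 0.394 or 0.381; power = Φ(0.577) = 71.8% or Φ(0.668) = 74.8%

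| ICC (assumed) | 70/260, 8 control units | 70/260, 11 control units |
|---|---|---|
| 0 | 84.4% | 84.4% |
| 0.01 | 81.8% | 82.4% |
| 0.02 | 79.2% | 80.5% |
| 0.05 | 71.8% | 74.8% |
| 0.10 | 61.4% | 66.4% |

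**4. The ICC at which 80% is lost.** For 80%, SE² may be at most 1/7.849 = 0.1274, which is 0.02039 after division by 6.25. With 8 control units: (0.02039 − 0.01813)/(0.1528 − 0.0181) = 0.017. With 11: 0.00225/(0.1187 − 0.0181) = 0.022.

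**5. The planned total.** 750 × 0.65 = 487.5, split 70:260, is about 103 and 384 analysed. At SD 2.5, power is 95% at ICC 0, 82–85% at ICC 0.05 and 69–75% at ICC 0.10 (8 and 11 control units).

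**6. A smaller true SD.** With total SD 1.6 and ICC 0.10 at 70/260, SE = 1.6 × √(1.775/70 + 1.622/260) = 0.284 and power is 94.0%; with 11 control units it is 96.1%.

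**The case against.** The strongest reply is that 2.5 is itself a deliberate multicenter allowance. It multiplies the earlier variance by 6.25/2.56 = 2.4 to 6.25/1.96 = 3.2, more than the control-arm design effect of 1.5 to 1.8 at ICC 0.10. Applying a design effect on top may count municipality variance twice. This stands in part: step 6 shows that the sample copes well if the true total SD is near 1.6. But that is a different assumption from the one the section makes, and the cover would come from a generous SD, not from a calculation that fits the allocation.

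Second, the planned effectiveness analysis uses repeated measures and controls stable municipality differences, so the ICC that matters concerns change rather than level. That also stands. It makes the percentages illustrative, but does not justify assuming an ICC of zero.

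Third, the three divided municipalities contribute to both arms, and their municipality effects partly cancel. The calculation ignores this. In the other direction, unequal cluster sizes, or a t reference on few clusters (about 70% at ICC 0.05 with 8 control units), would lower power.

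A reader might infer stronger points that the document does not support:
- *The design fails to reach 80%.* No ICC is given, and at ICC 0.01 power is still about 82%.
- *The whole rise from 1.4 to 2.5 is between-municipality variance, an ICC of 0.69.* The article does not say that 1.4 is a within-municipality SD. Individual variation could also rise, since any adult over 18 is eligible and the earlier study was in older adults.
- *The arithmetic is wrong.* 70/260 against 63/234 errs on the safe side, and 107 against 70/0.65 = 107.7 is rounding.
- *507 and 750 conflict.* A planned total above a stated minimum is no contradiction.

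**Conclusion.** The point holds as a defect of method with a conditional consequence. The section states 80% power from a calculation for independent participants in a trial allocated by municipality or zone, and the enlarged SD does not repair that. At SD 2.5 the slack is used up at an ICC of about 0.017 to 0.022; an ICC of 0.05 costs roughly 10 to 13 points against the 84% at ICC 0, and 0.10 costs 18 to 23.

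The size of the loss depends on an ICC that the document does not give, on SD 2.5 being the true total SD, and on equal cluster sizes. The planned 750 keeps power above 80% at ICC 0.05 but not at 0.10. The statement should be corrected, but the consequence is too uncertain, and too much offset by the larger planned sample and possibly generous SD, to rank as something that must be fixed.

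**What to change.** Rewrite the sample size paragraph to:

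- give the number of allocation units per arm, saying how the three divided municipalities are counted;
- state an assumed ICC range, for example 0.02 to 0.10, and apply 1 + (m − 1) × ICC in each arm;
- use an SD that does not also absorb between-municipality variance, or give the within- and between-municipality components separately;
- quote power for both the 507 minimum and the planned 750, after dropout.

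The cost is one paragraph and a stated power that may look less favourable. No added enrolment and no change to the design is proposed.

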### Statistical analysis

The data are suitable for multilevel or hierarchical modeling. Individuals are nested within municipalities and municipalities will be treated as fixed effects when mixed-effects models are applied.

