### Analysis of effectiveness

To evaluate whether the effect of the intervention varies according to the type of health problem(s), sociodemographic characteristics and home municipality will be used in linear mixed-effects models. Given the multilevel structure of the data (individuals over time within municipalities), we will control for stable differences between municipalities using a so-called fixed-effects model. Hence, we will control for time-invariant independent variables at the municipality level, such as the size of the municipality, demographics, and resources. In addition, the effect sizes will be calculated by dividing the difference of the mean change in the intervention groups and control groups by the standard deviation of the pretreatment scores.

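### Municipality is fixed in the models although 41 of 44 municipalities hold only one arm: a level comparison would rest on three municipalities, and a change comparison leaves municipality variation in change unmodelled

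*Protocol article*

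**What the plan says.** **Model.** The Statistical analysis section of the protocol article states that "municipalities will be treated as fixed effects when mixed-effects models are applied". Analysis of effectiveness repeats the choice in its own terms: "we will control for stable differences between municipalities using a so-called fixed-effects model". The reason offered there is the nesting of repeated measurements on participants inside municipalities. The stated purpose is that "we will control for time-invariant independent variables at the municipality level", with municipality size, demographics and resources named as examples. The same section uses these models to ask whether the effect varies by health problem, sociodemographic characteristics and home municipality, and it defines effect sizes from the difference in mean change between groups.

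**Allocation.** Design and setting describes 44 municipalities, of which eight serve as controls. A separate arrangement covers the divided ones: "for three municipalities with two zones, one will be assigned to the control group and the other to the intervention group". Allocation was not random, and the article explains how the zones were assigned: "The allocation of zones to the intervention or control group was based on practical reasons and decided by the municipality".

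The article states no random municipality effect, no municipality-by-time term and no cluster-robust variance.

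**The concern.** In 41 of the 44 municipalities, arm is itself a stable municipality-level characteristic. A model that removes all such characteristics therefore removes the treatment contrast in those municipalities, unless the effect is defined as a difference in change over time.

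If it is so defined, fixed intercepts leave a second gap. They take out stable differences in level, but not differences between municipalities in how much their participants change. Treatment is assigned to the whole municipality or zone, so those differences belong in the standard error of the treatment effect. If they are left out, each participant counts as an independent replicate of an allocation that was made only 8 to 11 times on the control side.

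The article expects such variation. The section on the control intervention says that standard care will differ among municipalities, and the Discussion says the same of reablement.

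At stake is either the precision of the main comparison or the honesty of its p-value and confidence interval.

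**Working it through.** **Inputs.** From Design and setting: 44 municipalities, eight control, three split into two zones, about 750 participants. From Sample size calculation: SD 2.5 (1.4 and 1.6 in an earlier study), difference 1 point, two-sided 5%, power 80%, 70 + 260 evaluable, 35% dropout, 107 + 400 = 507 enrolled. Assumed: equal recruitment over allocation units, and ICC of change 0.01 to 0.10.

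**The plan's own figure.** SE = 2.5 × √(1/70 + 1/260) = 0.337, so power = Φ(1/0.337 − 1.96) = 84%. The stated inputs need only 63 + 234 at that ratio, so 70 + 260 is slightly generous. The dropout step holds to rounding: 70/0.65 = 107.7 and 260/0.65 = 400. The calculation contains no clustering term.

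**Units.** Single-arm municipalities: 44 − 3 = 41, whether or not the eight controls include the three split ones. Allocation units: 41 + 2 × 3 = 47. Control units: 8 if the split municipalities are among the eight (5 + 3), and 11 if they are additional (8 + 3).

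**Case A: effect on follow-up level, with municipality dummies.**
- The 41 single-arm municipalities give 41 dummies plus an arm column: 42 columns, rank 41, so arm is aliased.
- Adding the three split municipalities gives 45 columns of rank 45. Arm is estimable, but only from those three.
- Evaluable per arm in three zones: 3 × 507 × 0.65/47 = 21, or 3 × 750 × 0.65/47 = 31.
- SE = SD × √(2/n), and power = Φ(1/SE − 1.96):

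| SD | n = 21 per arm | n = 31 per arm |
|---|---|---|
| 2.5 | SE 0.77, power 25% | SE 0.63–0.64, power 35% |
| 1.6 | SE 0.49, power 53% | SE 0.41, power 69% |
| 1.4 | SE 0.43, power 64% | SE 0.36, power 80% |

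The lower SDs are shown because the article raised its SD to 2.5 in expectation of more variation across 44 municipalities, and dummies would remove the level part of that. Using 1.4–1.6 as the within-municipality SD is an assumption.

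**Case B: arm-by-time (difference in change).**
- The 41 single-arm municipalities alone give 41 dummies, time and arm-by-time: 43 columns, rank 43. The contrast is estimable without the split municipalities.
- With m evaluable participants in every unit, the true variance of the contrast exceeds the one that ignores units by D = 1 + (m − 1) × ICC. Here m = 507 × 0.65/47 = 7, or 750 × 0.65/47 = 10.
- The actual type I error of a nominal 5% test is 2 × [1 − Φ(1.96/√D)]:

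| ICC of change | D, m = 7 | Type I error | D, m = 10 | Type I error |
|---|---|---|---|---|
| 0.01 | 1.06 | 5.7% | 1.09 | 6.1% |
| 0.02 | 1.12 | 6.4% | 1.18 | 7.1% |
| 0.05 | 1.30 | 8.6% | 1.45 | 10.4% |
| 0.10 | 1.60 | 12.1% | 1.90 | 15.5% |

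Simulation with 11 control and 36 intervention units gives about 5–6%, 6–7%, 8–10% and 11–15%, and about 5% at ICC 0.

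**Effect variation by home municipality.** This needs both arms within a municipality. It cannot be estimated in the 41 that have only one.

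**The case against.** - **The level comparison is probably not what is planned.** The effectiveness section speaks of individuals followed over time, of time-invariant municipality variables and of mean change. That reads as a difference-in-differences analysis, which is estimable everywhere. The only follow-up comparison named, the analysis of covariance under Descriptive statistics, has no stated municipality term for arm to be absorbed by. This stands. A reader might infer that the plan can estimate the effect only in three municipalities, or discards most of them; the documents do not support that, and Case A is conditional.
- **The mixed model may serve only effect modification.** The opening sentence of the effectiveness section says so. But the Statistical analysis section applies the fixed effect whenever mixed models are used, the Abstract describes the mixed models more generally, and no other analysis is said to account for municipality. This objection stands only in part.
- **Fixed effects are a reasonable defence in a non-randomised study.** This stands. They remove stable municipality confounding from the estimate of change and need not be given up.
- **Exact model terms belong in the analysis plan.** That is true of missing detail. Here the article makes a stated choice and gives its rationale, and that choice does not fit its allocation scheme.
- **The ICC is unknown.** This stands. At 0.01–0.02 the error rate is close to nominal, so the size of the problem in Case B is uncertain.

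**Conclusion.** The point holds in a limited form. The stated rule of fixed municipality effects does not fit allocation by municipality. Any level comparison made with it would have power well short of 80% at the planning SD, and would approach 80% only with the smaller SD and the larger enrolment. On the more natural reading, a comparison of change, the effect is estimable in all municipalities and stable differences are properly removed, but the standard error omits municipality variation in change. That omission is slight at an ICC of 0.01–0.02 and material from 0.05 upward. These figures rest on equal recruitment over 47 units, 35% dropout and the assumed ICCs.

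A reader might infer that neither version can answer the primary question validly. The documents do not support that. The level comparison would be imprecise rather than invalid, and in the change comparison it is the uncertainty, not the removal of stable differences, that is at fault. This should be fixed, but it does not undermine the design.

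**What to change.** 1. State the arm-by-time contrast (difference in change) as the treatment effect.
2. Keep municipality fixed intercepts if wished, to control stable differences. Add a random allocation-unit-by-time effect, where the unit is the municipality, or the zone in the three split ones, and a participant random effect, with Satterthwaite or Kenward-Roger degrees of freedom. Alternatively, use cluster-robust standard errors by allocation unit with a small-sample correction.
3. Do not estimate an arm effect on follow-up level in a model with municipality dummies.
4. Drop home municipality as an effect modifier, or report only the between-unit variance in change.

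The cost is analysis wording, with no new data. Confidence intervals will be wider: the standard error grows by √D, which is about 3–4% at ICC 0.01 and 26–38% at ICC 0.10 for 7–10 participants per unit.

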### Participants

The analysis will include all participants who answer the questionnaire both at baseline and follow-up, even if they drop out of the intervention (intention-to-treat analysis). *P*-values will be two-sided and significant at *P* ≤ 0.05.

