**Methods/Design:**

The study is a multicenter controlled trial. In total, 44 Norwegian municipalities will participate, including eight municipalities as a control group. For three municipalities with two zones, one will be assigned to the control group and the other to the intervention group. The experimental group will be offered reablement and the control group standard treatment. The sample will comprise approximately 750 participants. People will be eligible if they are home-dwelling adults, understand Norwegian, and have functional decline. Participants will be assessed at baseline, and after 10 weeks, 6 months, and 12 months. The primary outcome will be activity and participation measured by the Canadian Occupational Performance Measure. Physical functioning will be measured by the Short Physical Performance Battery and health-related quality of life by the European Quality of Life Scale. Coping will be measured by the Sense of Coherence questionnaire and mental health by the Mental Health Continuum Short Form. Costs will be generated based on registered working hours in different professions. Data analyses will be performed according to intention to treat. Univariate analysis of covariance will be used to investigate differences between the groups at baseline and the end of intervention. The data will be organized into two levels using a multilevel structure, i.e., individuals and municipalities, which will be analyzed using linear mixed-effects models. The working hours data (panel data) will be analyzed with random mixed-effects regression models. The cost-effectiveness of reablement will be evaluated according to the incremental cost-effectiveness ratio and uncertainty will be explored via the bootstrap method.

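### The analysis called intention to treat is limited to people who answer at baseline and at an unspecified follow-up, so it is an available-case analysis

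*Protocol article*

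**What the plan says.** The Methods/Design part of the abstract states: "Data analyses will be performed according to intention to treat". The Participants paragraph under Statistical analysis then says who is analysed: "The analysis will include all participants who answer the questionnaire both at baseline and follow-up", and adds "even if they drop out of the intervention (intention-to-treat analysis". So the set keeps people who leave the intervention, provided that they respond. Follow-up is not tied to 10 weeks, 6 months or 12 months, although Table 2 schedules the outcomes at all three.

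The Sample size calculation enlarges the groups for "the possibility of a relatively high dropout rate (up to 35 %) due to frail participants". The same section says that "the allocation of participants to the intervention group or control group will not be randomized".

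The Analysis of effectiveness section plans linear mixed-effects models for individuals over time within municipalities. The only other remark on missing values, in the Discussion, concerns checking incoming data and correcting them where possible. Nothing in the article returns people without a follow-up answer to the analysis.

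**The concern.** Intention to treat means that people are analysed in the group to which they were allocated, whatever happens later. The stated rule meets half of this: stopping the intervention does not remove anyone. The other half fails, because membership of the set depends on answering after allocation.

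This matters for three reasons. The loss being planned for is large. The reason given for it is frailty, which is plausibly connected with functional outcomes. And the Discussion rests causal interpretation on similarity of the groups at baseline, with statistical control of any differences; loss after baseline can undo that similarity among those who remain. Loss could also differ by arm: reablement ends within 10 weeks while standard treatment may continue, so contact with services may differ at 6 and 12 months. A reader who sees the intention-to-treat label would assume a protection that the set does not give.

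**Working it through.** **Inputs from the Sample size calculation:** 70 control and 260 intervention participants before dropout; 107 and 400 after; dropout up to 35%; SD 2.5; target 1 point; two-sided 5%; power 80%. The gaps used in step 4, and any loss rate other than 35%, are assumptions that stand nowhere in the documents.

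**1. The plan's inflated figures.** N/(1 − d) with d = 0.35:
- intervention: 260/0.65 = 400, as stated
- control: 70/0.65 = 107.7, which rounds up to 108; 107 is stated

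The figures reproduce to within one person. The inflation treats the 35% as lost to the analysis, in line with the rule in the Participants paragraph.

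**2. The base figures.** n(control) = (1 + 1/r) × (1.960 + 0.842)² × SD²/target², with r = 260/70 = 3.71. This gives 1.269 × 7.85 × 6.25 = 62.3, so 63 controls and 234 intervention participants. The stated 70 and 260 are about 11% larger and give about 84% power. This errs on the safe side and does not affect the point.

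**3. People who could be left out at minimum enrolment.** 0.35 × 107 = 37.45, so 37 controls; 0.35 × 400 = 140 intervention participants. These are ceilings.

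**4. Possible bias.** Let A be the mean change of answerers, N that of non-answerers, d the fraction lost, and gap = A − N. The mean for everyone is (1 − d)A + dN = A − d × gap, so answerers overstate their arm's mean by d × gap. For the contrast of intervention (I) minus control (C):

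bias = d_I × gap_I − d_C × gap_C

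| Loss I / C | Gap I / C (points) | Bias (points) |
|---|---|---|
| 35% / 35% | 1 / 1 | 0.35 − 0.35 = 0 |
| 35% / 20% | 1 / 1 | 0.35 − 0.20 = 0.15 |
| 20% / 35% | 1 / 1 | 0.20 − 0.35 = −0.15 |
| 35% / 35% | 1 / 0.5 | 0.35 − 0.175 = 0.175 |
| 35% / 35% | 1 / 0 | 0.35 − 0 = 0.35 |

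Bias is proportional to the gaps, so doubling both gaps in a row doubles its result. The direction depends on which arm loses more and on the sign of the gaps.

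**5. What the inflation protects.** Enrolling 107 and 400 brings the expected number of answerers back to about 70 and 260, and so protects power. Sample size does not appear in the bias formula, so enrolling more people does not reduce the bias.

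**The case against.** The strongest reply is that the set is sensible and only the name is wrong. Several parts of that reply stand.

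- The set is not per-protocol. A reader might infer that people who fail in reablement and leave it are removed. The text says the opposite: they stay if they answer. Only non-response excludes.
- A reader might infer that 35% of the cohort, or about 260 of 750 (0.35 × 750 = 262.5), will be dropped. The 35% is a planning maximum, and the article does not split it into leaving the intervention and not being assessed. If any one follow-up answer qualifies, only people with no follow-up at all are excluded, possibly far fewer.
- The planned mixed models can use partial follow-up. Under the lenient reading, the people lost are those with baseline only. They add nothing to a model that conditions on the baseline score; they contribute only if baseline is modelled as part of the outcome.
- Frailty is given as the reason for dropout. That it predicts change on the Canadian Occupational Performance Measure is inference, and with equal loss and equal gaps the bias is zero.
- A reader might infer that everyone who dies is left out of the QALY analysis, although the article gives death the value 0. The documents do not support this. Someone who answers at 10 weeks and dies later can meet the rule, and the cost-effectiveness section refers only to standard methods.
- The full missing-data method may sit in an analysis plan that is not shown, so its absence is no finding.

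None of this repairs the label. The article itself states the rule and calls it intention to treat.

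**Conclusion.** The point holds as a mismatch between label and set. The abstract and the Participants paragraph claim intention to treat, while the stated rule gives an available-case (assessment-completer) set, with an undefined follow-up visit. With up to 35% loss allowed for and no randomisation, differential loss could bias the comparison.

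Whether it will, and by how much, cannot be known from the documents. The illustrative sizes run from 0 to 0.35 points in either direction against a 1-point target. The upper figure needs the maximum loss rate and a 1-point gap confined to one arm. What can be said firmly is that the set depends on an event after allocation and that the wording hides this.

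**What to change.** Define the primary analysis set as all enrolled participants, by the arm of their municipality or zone. Fit the longitudinal mixed model already planned, by maximum likelihood, to all available scores from baseline to 12 months. Treat baseline as part of the outcome vector so that people with baseline only can contribute. Include baseline variables already listed in Table 2 that may predict dropout, such as age, physical performance, main health challenge and EQ-5D. Add a missing-not-at-random sensitivity analysis that shifts the assumed outcomes of non-answerers separately by arm. State which visit or visits follow-up means. Report the present rule as an available-case sensitivity analysis, and stop calling it intention to treat.

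The cost is a change of wording and a little more analysis work. Bias that the observed data do not explain may remain, which is why the sensitivity analysis is needed. Any explicit handling of deaths would need vital status or date of death, which Table 2 does not list.
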